### Intervention description {11a}

After confirming eligibility based on the inclusion/exclusion criteria, the target knee (left or right) for evaluation will be selected. If only one knee meets the criteria for PFP, that knee will be selected. If both knees qualify, the knee with greater pain will be chosen. All subsequent evaluations will be conducted on the knee selected as the target knee for assessment.

The investigational medical device “MORA Cure PFP” used in this study will be applied only to participants assigned to the treatment group. MORA Cure PFP consists of a web platform for healthcare professionals and a mobile application for patients. The investigator prescribes treatment through the healthcare web platform, and participants install the application on their mobile phones to begin therapy. At baseline, the investigator will randomize and enroll participants. For those assigned to the treatment group, the investigator will register them on the healthcare web platform and prescribe the device. Upon prescription, an installation code for the patient app will appear on the web platform. Participants will then follow the installation manual to install the app, agree to the terms of service, complete registration, and start the plan, with the Day 1 program beginning on the same day. The device provides an 8-week program of rehabilitative exercise and cognitive behavioral therapy (CBT) for PFP (Fig. 2). After the initial 8-week treatment period, participants can retain access to the device for up to 12 weeks.

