### Participant timeline {13}

Participants in this clinical trial will complete 4 to 5 outpatient visits: V1 (Screening), V2 (Baseline), V3 (In-treatment), V4 (Post-treatment), and V5 (Follow-up). V2 must occur within 4 weeks of V1 and may be conducted on the same day as V1. V3 is scheduled 4 weeks after V2, with an allowable range of 3 to 5 weeks. V4 is set for 8 weeks after V2, with a window of 8 to 9 weeks, and V5 is scheduled 12 weeks after V2, with an allowable range of 12 to 13 weeks. See Table 2 for the specific schedule of assessments for each visit. For Visit 3, participants may not need to visit the medical institution in person. In this case, certain checks, such as prior medication, concomitant medication, and adverse event assessments, may be omitted. Pain intensity assessment and the Kujala evaluation will be conducted by sending a survey link to the participant, who will complete it while in contact with the clinical trial site representative over the phone.

**Table 2 Tab2:** Assessment schedule by visit

Schedule	Screening (V1)	Baseline (V2)^1^	In-treatment (V3)^2,3^	Post-treatment (V4)^4^	Follow-up (V5)^5^
	− 4 weeks ~ 0 week	0 week	3 weeks ~ 5 weeks	8 weeks ~ 9 weeks	12 weeks ~ 13 weeks
Informed consent	X				
Screening number assignment	X				
Demographics	X				
Medical history	X				
Height and weight measurement		X			
Physical examination	X	X	X^3^	X	X
Concomitant/previous medication history	X	X	X^3^	X	X
Knee X-ray Imaging and K-L grading	X^6^				
Inclusion/exclusion criteria review	X	X			
Selection of target knee (L/R)		X			
Randomization and assignment of registration number		X			
Pain intensity assessment		X	X	X	X
Kujala questionnaire		X	X	X	X
EQ-5D-5L questionnaire		X		X	X
PHQ-9 questionnaire		X		X	X
PCS questionnaire		X		X	X
Overall perceived recovery score assessment				X	X
Disease education		X			
Investigational device prescription and app installation (treatment group only)		X			
Education on self-exercise (control group only)		X			
Self-exercise patient diary distribution (control group only)		X			
Self-exercise patient diary return (control group only)			X^7^	X^7^	X
Adverse event review		X	X^3^	X	X
Investigational device app deletion (treatment gropu only)					X

1. V2 must be conducted within 4 weeks of V1, and V1 and V2 can take place on the same day

2. V3 is conducted 4 weeks after V2, with a permissible variation of one week before or after (3 to 5 weeks)

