### Outcomes {12}

The primary efficacy outcome of this trial is usual pain intensity score (VAS, 100 scale) at 8 weeks (V4). For secondary outcomes, see Table 1. For the method of aggregation, all outcome measures will be analyzed as continuous variables using mean values with appropriate statistical comparisons between groups (For further detail, see Statistical Analysis).

Through interviews, demographic information, medical history, surgical history, and prior/concomitant medications will be collected. Physical examination will include measurements of height, weight, and a patella examination. A knee X-ray will be taken to assign a K-L grade [40], which is used to assess exclusion criteria for osteoarthritis.

The usual and worst pain intensity scores assess the average and peak knee pain experienced over the past week, respectively. Participants mark their pain level on a visual analog scale from 0 to 100, with values recorded and rounded to the nearest whole number [41].

To assess knee function, participants complete the anterior knee pain scale (Kujala score), 13-item self-report questionnaire [42], with a total score calculated from the responses. Quality of life is assessed via the EQ-5D-5L [43] questionnaire, recording the sum of scores across five questions and today’s health status score. Depression severity is evaluated using the Patient Health Questionnaire-9 (PHQ-9) [44], with a total score from nine questions, while pain catastrophizing is assessed using the Pain Catastrophizing Scale (PCS) [45], totaling scores from 13 questions. Participants also rate their perceived recovery level on a 0 to 6 scale [46].

All pain and questionnaire assessments are conducted as electronic patient-reported outcomes (ePRO). Participants use digital tools provided at the site, with data automatically transferred to the electronic case report form (eCRF). For visit 3, if conducted as a televisit, participants may complete the assessments remotely.

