### Sample size {14}

The primary efficacy variable of this clinical trial is the intensity of usual pain over the past week at 8 weeks post-treatment initiation, aiming to assess whether the experimental group shows superior improvement compared to the control group. The hypothesis for the superiority test on the primary efficacy variable is as follows: $${H}_{0}: {\mu }_{t}={\mu }_{c} vs. {H}_{1}: {\mu }_{t}\ne {\mu }_{c}$$, where $${\mu }_{t}$$ represents the usual pain intensity at 8 weeks for the experimental group, and $${\upmu }_{\text{c}}$$ represents the same for the control group.

The sample size was calculated based on prior study of MORA Cure PFP (ClinicalTrials.gov., NCT05614583). In the exploratory clinical trial, the usual pain over the past week of full analysis set at 8 weeks post-treatment was 2.31 ± 1.49 for the experimental group and 3.18 ± 2.43 for the control group [35]. The calculated effect size (Cohen’s *d*) is as follows: $$d=\frac{{m}_{t}-{m}_{c}}{\sqrt{\left({s}_{t}^{2}+{s}_{c}^{2}\right)/2}}=\frac{2.31-3.18}{\sqrt{\left({1.49}^{2}+{2.43}^{2}\right)/2}}=-0.428$$, where $${m}_{t}$$ is mean of the experimental group, $${m}_{c}$$ is mean of the control group, $${s}_{t}$$ is standard deviation of the experimental group, and $${s}_{c}$$ is standard deviation of the control group [47]. Values were used up to the second decimal place, and the effect size was calculated without rounding.

Using an effect size of − 0.428, a Type I error of 0.05, and a power of 0.8, the formula for calculating the sample size per group is: $$n=\frac{2{\left({z}_{1-\alpha /2}+{z}_{1-\beta }\right)}^{2}}{{\left(d\right)}^{2}}=\frac{2{\left(1.960+0.842\right)}^{2}}{{\left(0.428\right)}^{2}}=86$$, where $$n$$ is required sample size per group (rounded up to the nearest whole number), $$\alpha$$ is Type I error, $$\upbeta$$ is Type II error (1 − power), and $$d$$ is effect size [47].

Considering a typical dropout rate of 10–30% for clinical trials involving digital services [48], a 20% dropout rate was assumed for this study. Adjusting for this dropout rate, the required sample size per group is calculated as: $${n}^{\text{'}}=86\times \frac{1}{1-r}=107.5$$, where *r* is the dropout rate (0.2). Thus, the target sample size is set at 216 participants in total, with 108 per group (Fig. 1).

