### Plans to promote participant retention and complete follow-up {18b}

Participants will receive 50,000 won (equivalent to 26 US dollars) per visit as transportation reimbursement. If Visit 1 and Visit 2 are conducted simultaneously, participants will receive double the amount, and the same amount will be provided for Visit 3, even if it is an electronic visit. At each visit, the investigator will check and monitor the treatment progress (automated data from the app for the treatment group, patient diaries for the control group). The application includes a notification feature that allows reminders to be sent at the patient’s preferred time, and personalized messages are sent based on exercise compliance to help motivate the patient.

To meet regulatory requirements and ensure study integrity, data from participants who leave or are withdrawn from the trial will be collected, recorded, and retained for the period during which they participated in the study.

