### Methods in analysis to handle protocol non-adherence and any statistical methods to handle missing data {20c}

For the analysis of the FAS, missing values occurring after treatment that are used for primary and secondary efficacy evaluation variables will be imputed using the last observation carried forward (LOCF) method. However, when imputing missing values, results prior to the administration of the investigational medical device will not be substituted for post-administration results. Other data will be analyzed as collected (available data) without imputation.

For the analysis of the PPS, missing values will not be imputed and will be analyzed as collected.

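### LOCF in the primary analysis fills a missing week-8 pain score with a mid-treatment one, so the primary result is biased if those participants would have changed after week 4 and dropout or that change differs by arm

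*Protocol article*

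**What the plan says.** The missing-data section {20c} of the protocol article states that, in the full analysis set (FAS), missing post-treatment values of the primary and secondary efficacy variables "will be imputed using the last observation carried forward (LOCF) method". It adds that "results prior to the administration of the investigational medical device will not be substituted for post-administration results". The section on analysis sets makes the FAS the primary efficacy set, and section {20a} specifies ANCOVA with the baseline value as covariate, two-sided at 0.05.

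The primary outcome is usual pain on a 0–100 VAS at week 8 (V4). Table 2 schedules pain at V2, V3, V4 and V5. Section {13} says "V3 is scheduled 4 weeks after V2, with an allowable range of 3 to 5 weeks" and "V5 is scheduled 12 weeks after V2, with an allowable range of 12 to 13 weeks". Section {11a} says "The device provides an 8-week program of rehabilitative exercise and cognitive behavioral therapy (CBT) for PFP".

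On dropout, section {14} begins "Considering a typical dropout rate of 10–30% for clinical trials involving digital services" and then assumes 20% overall. Section {18b} describes app reminders and says "personalized messages are sent based on exercise compliance to help motivate the patient". The only other stated efficacy analysis is the per-protocol set (PPS), without imputation. It is limited to participants who did not withdraw early, had no major violations and reached at least 50% compliance.

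**The concern.** With baseline barred, V3 is the only possible donor for a missing week-8 pain score. LOCF then assumes that a participant who misses V4 would have had the same pain at week 8 as midway through treatment. The ANCOVA gives the filled value the weight of a measured one. Because values are carried only forward, a participant who misses V4 but attends V5 has the week-12 score ignored when week 8 is filled.

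The same rule fills a missing week-12 pain or Kujala score from week 8, or from week 4 if week 8 is also missing.

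It has no donor at all for 15 of the 35 secondary endpoints in Table 1. EQ-5D-5L, PHQ-9 and PCS are not taken at V3, perceived recovery is first taken at V4, and nothing post-treatment precedes week 4. These endpoints become complete-case analyses beside 20 that can be imputed.

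At stake is the single confirmatory test. Depending on who drops out and how they would have fared, LOCF can raise the false-positive rate or hide a real effect.

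**Working it through.** **The plan's own figure.** 2 × (1.960 + 0.842)² / 0.428² = 85.7, rounded up to 86 per group. 86 / (1 − 0.2) = 107.5, so 108 per group and 216 in total. The stated sample size reproduces. At 20% dropout, up to 0.20 × 108 ≈ 22 week-8 scores per arm could be week-4 values.

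**Bias formula.** Let p be the share of an arm's analysed participants whose week-8 score is carried from week 4. Let D be the fall in pain from week 4 to week 8 that those participants would have had. Then

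bias towards the app = p_control × D_control − p_app × D_app.

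This is zero if D = 0 in both arms, and its sign reverses if D is negative (worsening).

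**Inputs that the article does not give (assumed).** SD 20 on the 0–100 scale; the pilot SDs pool to √[(1.49² + 2.43²)/2] = 2.016, which look like a 0–10 scale and are multiplied by 10. Correlations are 0.5 (baseline–week 4), 0.4 (baseline–week 8) and 0.7 (week 4–week 8). There are 108 per arm, and dropout is unrelated to outcome within arm. D is 5, 10 or 15 points. False-positive rates come from simulated ANCOVA on LOCF data (4,000 trials per setting).

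**No true effect, same D in both arms.** Dropout is shown as app v control.

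| Dropout | Timing | Net gap in p | Bias towards app at D = 5 / 10 / 15 | False-positive rate |
|---|---|---|---|---|
| 15% v 25% | all between V3 and V4 | 0.25 − 0.15 = 0.10 | 0.5 / 1.0 / 1.5 | about 5–8% |
| 10% v 30% | half before V3 | 0.15/0.85 − 0.05/0.95 = 0.124 | 0.6 / 1.2 / 1.9 | about 5% / 8% / 10% |
| 10% v 30% | all between V3 and V4 | 0.30 − 0.10 = 0.20 | 1.0 / 2.0 / 3.0 | about 7% / 12% / 21% |

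In the second row, participants lost before V3 have no donor and leave the analysis. In the same settings a likelihood repeated-measures analysis stays at about 5%.

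**Cross-check on the pilot scale.** SE = 2.016 × √(2/108) = 0.274. With D = 1.0 and 10% v 30%, the bias is 0.20, or 23% of the planned 0.87. The two-sided type I error is 0.113 by normal approximation and 0.128 by simulation. With D = 0 it stays at about 0.05.

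**True effect of 8.7 points (0.87 × 10), half present at week 4.** The control arm gains 10 points between weeks 4 and 8, so the app arm gains 10 + 4.35 = 14.35.

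- Equal 20% dropout: bias = 0.20 × 10 − 0.20 × 14.35 = −0.87, so LOCF estimates about 7.8. Power is 86%, against 90% for repeated measures.
- 30% app v 10% control: bias = 0.10 × 10 − 0.30 × 14.35 = −3.3, so LOCF estimates 5.4. Power is 55%, against 90%.

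**If dropouts would have lost ground.** With D = −1.0 on the pilot scale and 30% app v 10% control, bias = 0.10 × (−1.0) − 0.30 × (−1.0) = 0.20 towards the app.

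**Endpoints without a donor (Table 1 numbering).** 3–7 (five), 22–25 (four), 16–18 (three) and 33–35 (three): 5 + 4 + 3 + 3 = 15.

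**The case against.** Several points on the other side stand.

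- **Imbalance alone is not enough.** A reader might infer that any arm difference in dropout shifts the result, or that the arm with more dropout is always credited with less improvement. Neither follows. The bias is zero if dropouts would not have changed after V3, and it reverses if they would have worsened.
- **A bias towards the app is not shown.** Only the app sends reminders and motivating messages, but those messages concern exercise compliance. Both arms are paid per visit {18b}, receive support and feedback at visits {11c} and are contacted after a missed visit {11b}. Higher control dropout is possible but not established.
- **21% is not a forecast.** The 10–30% in section {14} is a range across digital-service trials. It is not a gap between these two arms, and the article does not time dropout. Starting from an assumed week-4 mean of 32, gains of 10 or 15 points put both arms at 22 or 17, below both pilot arms (23.1 and 31.8 after the factor of 10). Only the 5-point case sits near them. The bias depends on the change and not the starting level, however, and the pilot's week-4 level is not given, so this tempers the larger figures without ruling them out.
- **The PPS is specified, and discrepancies with the FAS will be investigated.** But it removes early withdrawals and low compliers, so it cannot show whether carrying their week-4 scores was sound.
- **Sensitivity analyses may sit in an analysis plan not shown.** Their absence here is no fault. The choice of LOCF as the primary method, though, is made in this article.
- **The alternative is not assumption-free.** The simulated dropout was unrelated to outcome within arm, which suits a likelihood model. Outcome-dependent dropout in an open-label trial could bias that model too.

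Finally, FAS entry requires post-randomization primary efficacy data without naming a visit. If that meant the week-8 score itself, nothing would be left to impute for the primary variable. That reading conflicts with section {20c}, which expressly imputes it.

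**Conclusion.** The concern holds in conditional form. The article fixes LOCF for the primary analysis, the only donor for week 8 is a mid-treatment score, and no stated analysis tests the no-change assumption. The assumption concerns only participants who miss V4. If they would have continued to improve, heavier control dropout favours the app and heavier app dropout hides its effect; if they would have worsened, the directions reverse. Equal dropout is not a safeguard either, because an effect still growing after week 4 is diluted.

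Under the assumptions listed, the inflation of the false-positive rate ranges from negligible to serious, and the top of that range is a worst case. The article supports neither a fixed direction nor a single size. LOCF is therefore neither unbiased nor reliably conservative for a confirmatory claim, and the method should be changed before database lock.

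**What to change.** In section {20c}, with a matching change in {20a}, replace LOCF as the primary method:

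- **Usual pain:** a mixed model for repeated measures on the observed scores at weeks 4, 8 and 12, with arm, visit, arm-by-visit, baseline, baseline-by-visit and unstructured covariance. The week-8 contrast between arms is the primary test.
- **Worst pain and Kujala:** the same model.
- **Outcomes measured only at V4 and V5:** a two-visit model, or multiple imputation drawing on baseline and the pain scores.
- **LOCF:** keep as a sensitivity analysis. Because the repeated-measures model assumes missing at random, a delta-adjusted (tipping-point) analysis is a useful companion.

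Cost: an amendment to the protocol and analysis plan before database lock, with the IRB and MFDS approval that section {25} requires, and some programming. Nominal power would be slightly lower (about 89% against 93% in simulation) if the full effect is already present at week 4 and dropout is equal. No extra participants, visits or data are needed.

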### Statistical methods for demographic and other baseline characteristics

The full analysis set (FAS) will be analyzed for demographic information, medication history, treatment history, and past/current medical history of participants. Categorical data (e.g., gender) will be presented as frequency and percentage within the safety population, while continuous data (e.g., age) will be summarized using descriptive statistics, including mean, standard deviation, median, minimum, and maximum values. Results will be reported separately for the experimental and control groups. Group comparisons will use a two-sample *t*-test for continuous variables (or Wilcoxon’s rank-sum test if normality is not met) and Pearson’s chi-square test for categorical variables (or Fisher’s exact test if more than 20% of cells have expected counts below 5).

Past and current medical history will be standardized using the latest the Medical Dictionary for Regulatory Activities (MedDRA) version, classified by system organ class (SOC) and preferred term (PT), with frequencies and percentages reported per group. Medication and treatment history will be standardized by the latest anatomical therapeutic chemical (ATC) classification, reported by level 1 (anatomical main group) and level 2 (therapeutic subgroup), and analyzed by Pearson’s chi-square test (or Fisher’s exact test where appropriate).

### Statistical methods for primary and secondary outcomes {20a}

For the definition of efficacy evaluation variables, see Table 1. Descriptive statistics (mean, standard deviation, median, minimum, maximum) will be presented for both experimental and control groups. Group differences will be analyzed using ANCOVA with baseline values as covariates, providing adjusted means (least square means), *p*-values, and 95% confidence intervals. Statistical tests will be two-sided with a significance level of 0.05, and results will include clinical interpretation.

Safety analysis will be conducted on the safety set. Adverse events (AEs) will be standardized by SOC and PT using the latest MedDRA version. Treatment-emergent adverse events (TEAEs) will be recorded as a single event per participant if they share the same SOC and PT, with severity classified by the highest severity reported, and causal relationship classified by the stronger link to the investigational device. Analysis will focus on TEAEs, including counts and percentages for TEAEs, knee-related TEAEs, adverse device effects (ADEs), and serious adverse events (SAEs). Percentage differences will be tested using Pearson’s chi-square test or Fisher’s exact test, if appropriate.

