### Adverse event reporting and harms {22}

All adverse events that occur or worsen after obtaining the subject’s consent will be collected, except for those who fail the screening. Pre-existing signs or symptoms at the time of consent are recorded in the medical history section of the CRF. AEs should be monitored until symptoms resolve and the condition stabilizes, and progress reports may be required by the sponsor. The investigator should provide a clear diagnosis, or otherwise record symptoms/signs. Appropriate examinations and treatments must be administered for all AEs. If an AE makes it difficult to continue the trial, the subject may drop out or the trial may be discontinued, with the best treatment provided for safety.

The CRF must record whether the AE is treatment-emergent (TEAE), the onset and end dates, severity, causal relationship with the investigational device, actions taken, and outcome. Serious adverse events (SAEs), serious adverse device effects, and unexpected adverse device effects must be reported to the IRB and regulatory authorities within the required timeframes. Specific AEs, such as worsening knee pain, cramps, dizziness, changes in mood or thought patterns, and any other significant AEs, must be documented and shared with the sponsor within 24 h.

All adverse events that occur will be standardized using System Organ Class (SOC) and Preferred Term (PT) with the latest version of MedDRA. Treatment emergent adverse events (TEAEs) that occur after application of the investigational medical device will be counted as one event when the same SOC and PT adverse event occurs multiple times in one subject, and when the severity differs for the same adverse event, it will be handled with the maximum severity. When the causal relationship differs for the same TEAE in one subject, it will be handled in the direction of higher relatedness to the investigational medical device. Summary and analysis of adverse events will be performed for TEAEs. The number of subjects experiencing events, incidence rates, and number of events will be presented for TEAEs, knee-related TEAEs, ADEs, and SAEs.

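### Adverse device effects are tested between arms although only the app arm can have one, so that comparison says nothing about relative safety

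*Protocol article*

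**What the plan says.** The safety paragraph under Statistical methods for primary and secondary outcomes {20a} names four categories, "including counts and percentages for TEAEs, knee-related TEAEs, adverse device effects (ADEs), and serious adverse events (SAEs". It continues: "Percentage differences will be tested using Pearson’s chi-square test or Fisher’s exact test, if appropriate". No category is taken out of that sentence, and ADEs are not marked as belonging to one arm.

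Adverse event reporting and harms {22} lists what the case report form (CRF) must hold for each event, including "severity, causal relationship with the investigational device, actions taken, and outcome". Where causality ratings for the same event differ within a participant, {20a} has the "causal relationship classified by the stronger link to the investigational device", and {22} repeats the rule: "it will be handled in the direction of higher relatedness to the investigational medical device". The device is the only causality reference that the article mentions.

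Intervention description {11a} says the device "will be applied only to participants assigned to the treatment group". The control group does self-guided exercise from paper materials. Under Definition of analysis sets, the safety set covers both arms: randomized participants with a record of using the device or of doing self-exercise.

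**The concern.** The stated objective is to evaluate safety and efficacy by comparison with conventional treatment, so a p-value for a safety category will be read as evidence on relative safety. For ADEs it cannot be that. One arm has the device and can have device effects. The other has no device and so has a count fixed at zero before the trial starts.

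Both arms exercise daily, and {22} itself singles out worsening knee pain and cramps as events to watch. A flare during app-guided exercise can enter the ADE row. A flare of the same kind and severity during paper-guided exercise cannot. A significant ADE difference would then be reported against the app even if the two exercise programmes did equal harm.

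The issue is attribution, not timing. Counting treatment-emergent adverse events (TEAEs) from randomisation in both arms would leave the control ADE count at zero.

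**Working it through.** **Arm size.** The article states no figure for the ADE test, so the only figure to reproduce is the arm size. From Sample size {14}, with the effect size as stated: n = 2 × (1.960 + 0.842)² / 0.428² = 85.7, rounded up to 86. With 20% dropout, 86 / 0.8 = 107.5, rounded up to 108 per group and 216 in total. This agrees with the article. I use 108 per arm, with 86 as a lower case.

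**Control count.** Device causality defines an ADE, and {11a} gives the device to one arm. The control entry is therefore 0/108 by definition.

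**Which test.** With k ADE participants in the app arm and none in control, the expected count is k/2 in two of the four cells. At k = 6 that is 3.0, so half the cells are below 5. The 20% rule that the article states for baseline comparisons would point to Fisher's exact test.

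**Fisher threshold.** With equal arms and all events on one side, the two-sided p is 2 × C(108, k) / C(216, k).

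- k = 5: 2 × (108/216 × 107/215 × 106/214 × 105/213 × 104/212) = 2 × 0.0298 = 0.060
- k = 6: multiply the bracket by 103/211, giving 2 × 0.01455 = 0.029

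Six ADE participants, 6/108 = 5.6%, are enough. At 86 per arm the threshold is also 6 (p = 0.0286; 5 give 0.0589). An uncorrected chi-square, X² = 216k / (216 − k), would cross 0.05 at k = 4 (864/212 = 4.08, p = 0.0435).

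**How often the threshold is reached.** With control fixed at zero, the probability is P(X ≥ 6) for X binomial with n = 108 (or 86) and true app-arm rate π. The article gives no π, so the rates below are assumptions. The last column shows the same Fisher test if events related to the allocated intervention were judged alike in both arms and the true rates were equal.

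| Assumed rate | Control fixed at 0, 108 per arm | Control fixed at 0, 86 per arm | Both arms judged alike, equal rates, 108 per arm |
|---|---|---|---|
| 2% | 2.2% | 0.8% | 0.6% |
| 3% | 10.7% | 4.5% | 1.3% |
| 5% | 45.6% | 26.0% | 2.3% |
| 8% | 87.1% | 69.4% | 2.8% |
| 10% | 96.5% | 87.1% | 3.0% |
| 15% | 99.9% | 99.3% | 3.2% |

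The first two result columns depend only on the app-arm rate. Nothing that happens in the control arm can change them.

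**The case against.** **The test is inferred.** Section {20a} has a general sentence after a list and does not name an ADE test. Section {22}, on the same four categories, says only that numbers and incidence rates will be presented. The unseen analysis plan may drop the test. This weakens the point but does not remove it. As written, the sentence covers the whole list, and its closing condition most naturally governs the choice between the two tests, not whether ADEs are tested.

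**A one-armed ADE count is not an error.** A device trial needs the category for reporting, and it is confined to the device arm by its nature. That is correct. The fault is the between-arm p-value, not the category.

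**Relative safety does not depend on ADEs.** This also stands. A reader might infer that harm from the control exercise is lost. The documents do not support that: {22} collects all events arising or worsening after consent, with dates, severity, actions and outcome, and control participants are in the safety set. A self-exercise flare would appear among the knee-related events. One condition applies. Section {22} describes TEAEs as occurring after application of the device, so they must be read as counted in both arms.

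**The CRF is not shown.** A reader might also infer that a control flare has to be coded as unrelated to treatment, or that no other relatedness item exists. The article names only device causality and does not rule out another item. The most that can be said is that attribution to the control exercise is not described.

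**The probabilities rest on assumed rates and are not type I errors.** Both parts are correct. At 2% the test is significant in only 2.2% of trials. If control ADEs are zero by definition and app ADEs are not, the ADE rates truly differ. The table shows that the test answers a question other than relative harm, not that it rejects a true null hypothesis about ADEs too often.

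**Conclusion.** The point holds in a limited form. The plan as written tests app-arm ADEs against a control count that is zero by definition, so the p-value carries no information on relative safety. Any significant result would go against the app. Six ADE participants of 108 suffice (Fisher p = 0.029), and the chance of reaching that number runs from 2.2% to 99.9% over assumed rates of 2% to 15%.

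This rests on two readings: that an ADE means an event related to the investigational device, and that the testing sentence in {20a} covers every category listed before it. It does not rest on any event rate, which affects only how often the problem would show.

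The primary efficacy analysis is unaffected. The all-cause safety comparisons remain usable if TEAEs are counted in both arms. The documents do not support the stronger conclusions that control-arm harm is unrecoverable or that a second causality field is required.

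**What to change.** In {20a}, limit the testing sentence to all-cause TEAEs, knee-related TEAEs and serious adverse events, counted in both arms, and state that the between-arm safety comparison rests on these. Add that ADEs are reported for the treatment arm only, as count, percentage and confidence interval, with no between-arm p-value.

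The cost is a sentence or two, settled before database lock. It needs no new data and gives up only a p-value that could not be interpreted. A change to the approved protocol would need institutional review board (IRB) and Ministry of Food and Drug Safety (MFDS) approval, as the article's amendment section says.

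Recording relatedness to the allocated intervention in both arms is an optional addition if the CRF can still be changed, with the device field kept for regulatory reporting. It is not clearly cheap. Recruitment began in April 2024 and was expected to end in December 2024, so events already recorded might have to be re-attributed. The judgement would also be made open-label, which makes it a weaker basis for comparison than the all-cause counts.
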